### Analyses

#### Quantitative analysis (phase 1)

Quantitative data will be coded and entered into the Statistical Package for the Social Sciences (IBM SPSS Statistics Version 24). Data on participant eligibility, recruitment, refusal, and retention will be assessed as proportions and rates. Demographic characteristics and adherence to the intervention components will be reported with descriptive statistics as appropriate, for instance, reporting of mean standard deviation (SD) for interval scale variables and frequency/percentages for categorical variables. Differences between control and intervention groups at baseline will be assessed using chi-squared tests and independent *t*-tests. Potential effective outcomes will estimate the effect size and be analysed for mean change using pair sample *t*-tests to compare the difference pre and post intervention, and repeated measure analysis of variance (ANOVA) to consider interactions. However, given that this is a feasibility study, no inferences will be made regarding statistical significance, given that the sample size is not powered to make such assertions. Data from the 3-day food diary will be entered into Nutritics for diet analysis to estimate dietary protein and energy intake. By using Nutritics software (www.nutritics.com - version 3.1), this will enable analysis of compliance with food-based dietary guidelines [63].

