**Sample:**

For phases 1 and 3, a total of 40 patient participants will be recruited (10 per intervention site and 10 per control site). For phase 2, qualitative data will be collected through interviews with approximately 15 patients and interviews or focus groups with 15 HCPs across all sites. Recruitment commenced on 08.09.25 following ethical approval (REC reference: 25/NI/0069).

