#### Randomisation

Cluster sites have been randomly placed in either the multimodal and standard care group (intervention group) or the standard care group (control group). Two sites have been randomised to intervention, and two have been allocated to control centrally using a computer-generated randomisation schedule (Nquery) independently by a statistician from Northern Ireland Clinical Trials Unit (NICTU). For pragmatic reasons, the personnel who will approach participants regarding the trial will have access to the random allocation sequence and participants will be made aware of their allocation.

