#### Processes

##### Recruitment (phase 1 and 3)

Our recruitment rate is anticipated to be two patients per month per site. The sample size for the feasibility study is 40 patients, collectively 20 per intervention arm, 20 per control arm, based on providing sufficient information to inform the primary outcomes [40]. The study is being supported by Northern Ireland Clinical Research Network (NICRN).

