#### Quantitative analysis (phase 3)

A cost-consequence analysis is recommended by the National Institute of Health Research for both complex interventions and feasibility studies where the outcomes of interest are not clear [68]. Costs and outcome measure data for both the intervention and control group will be presented using means and 95% confidence intervals to show a general overview of the economic costs of the intervention, and differences in resource use and outcome measures between groups. Completion rates and missing data for MODRUM [61] and the EQ-5D-5L [58] will be presented as frequencies to assess the feasibility of data collection.

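### The planned between-arm tests are patient-level although only four sites were randomised, so with any positive intracluster correlation they over-reject and patient-level intervals under-cover; the baseline tests should be dropped and arm comparisons should account for site.

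*Protocol article*

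**What the plan says.** All references are to the protocol article.

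- **Unit of randomisation** (Randomisation): "Two sites have been randomised to intervention, and two have been allocated to control centrally". The same section says that the staff who approach patients know the allocation.
- **Size** (abstract, Sample): "a total of 40 patient participants will be recruited (10 per intervention site and 10 per control site"). Recruitment (phase 1 and 3) gives the same total as "collectively 20 per intervention arm, 20 per control arm".
- **Baseline comparison** (Quantitative analysis, phase 1): "Differences between control and intervention groups at baseline will be assessed using chi-squared tests and independent" t-tests.
- **Outcomes** (same section): effect sizes, paired t-tests for pre-post change, and "repeated measure analysis of variance (ANOVA) to consider interactions".
- **Limit on inference** (same section): "However, given that this is a feasibility study, no inferences will be made regarding statistical significance". The reason given is that the sample is not powered for it.
- **Costs and outcome measures** (Quantitative analysis, phase 3): "Costs and outcome measure data for both the intervention and control group will be presented using means and 95% confidence intervals". The aim includes showing differences between groups. How the intervals are computed is not stated.

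The article mentions no site term, ICC, design effect or other allowance for clustering.

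**The concern.** The chi-squared test, the independent t-test and a standard repeated-measures ANOVA treat the 40 patients as independently allocated. They were not: treatment is a property of the site. Patients at one unit share staff, case mix and local practice, so their outcomes tend to be alike, and a patient-level standard error for an arm difference leaves that component out. The article itself expects sites to differ. Study setting presents the mix of patients and services as a strength, and Control arm and Strengths and limitations say that standard care may vary by site and will be recorded.

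This is a stated choice of method that does not match the stated design, not a detail left to a fuller document. Two things are at stake. Arm differences may look more precise than they are, in a study whose second objective is to inform the design of a definitive cluster trial. And a small baseline p-value cannot be interpreted: it may reflect site differences, selective recruitment by staff who know the allocation, or both, and the test cannot separate them.

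**Working it through.** **The plan's own figure.** 2 × 10 + 2 × 10 = 40, and 20 + 20 = 40. The sample size is consistent. There is no power, SD or ICC to reproduce.

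**Inputs.** From the article: 2 sites per arm and m = 10 patients per site. Assumed: ICC from 0 to 0.20. Results are in units of the outcome SD.

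**Formulas for one comparison at one time point.**
- Design effect: DE = 1 + (m − 1) × ICC = 1 + 9 × ICC.
- Nominal patient-level 95% half-width: t on 38 df × √(2/20) = 2.024 × 0.316 = 0.64 SD.
- Site-level 95% half-width from the four site means: t on 2 df × √(ICC + (1 − ICC)/10), with t = 4.303. Example at ICC 0.05: 4.303 × √(0.05 + 0.095) = 4.303 × 0.381 = 1.64 SD.

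**Simulation.** 200,000 trials per ICC, four sites of 10, normal outcome, no true difference. The patient-level columns refer to the independent t-test and its interval.

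| Assumed ICC | DE | Effective N (40/DE) | Patient-level 5% test rejects | Patient-level 95% interval covers | Site-level half-width (SD) | Ratio to 0.64 |
|---|---|---|---|---|---|---|
| 0 | 1.00 | 40.0 | 5.0% | 95.0% | 1.36 | 2.1 |
| 0.01 | 1.09 | 36.7 | 6.0% | 94.0% | 1.42 | 2.2 |
| 0.05 | 1.45 | 27.6 | 10.4% | 89.6% | 1.64 | 2.6 |
| 0.10 | 1.90 | 21.1 | 15.9% | 84.1% | 1.88 | 2.9 |
| 0.20 | 2.80 | 14.3 | 25.8% | 74.2% | 2.28 | 3.6 |

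The site-level t-test on 2 df held 5.0% throughout. A chi-squared test at an assumed prevalence of 50% rejected 4.2%, 5.3%, 9.7% and 15.5% of the time at ICC 0, 0.01, 0.05 and 0.10.

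**What the widening consists of.** The ratio in the last column is √DE × 4.303/2.024. The second factor, 2.13, is the price of having 2 df and is present even at ICC 0, where the patient-level interval covers correctly. Only √DE (1.04, 1.20 and 1.38 at ICC 0.01, 0.05 and 0.10) measures how far the patient-level standard error is too small: by 1 − 1/√DE, or 4%, 17% and 27%.

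**The ANOVA interaction.** The table does not carry over directly. A stable, additive site effect cancels from change over time, so the group-by-time interaction is distorted only if change itself varies by site. That was not simulated. The paired t-tests compare time points, not arms, and are not part of this point.

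**The case against.** The strongest reply is that little depends on these analyses. The article rules out inference on significance, the primary outcomes are recruitment and retention, and the Discussion rests progression on recruitment, compliance and acceptability. That stands, and it limits the harm to what is reported. It does not remove the mismatch. The disclaimer blames sample size rather than the four clusters, it sits uneasily beside planned significance tests at baseline, and it does not cover effect sizes or the phase 3 intervals.

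A reader might also infer more than the article supports:

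- *That the intervals are far too narrow.* This depends on an ICC that the article does not give. At 0.01, coverage is still 94%.
- *That 0.64 SD against 1.4 to 1.9 SD is the size of the error.* Most of that gap is the price of 2 df.
- *That no arm comparison could ever be significant.* With six possible allocations, the smallest two-sided permutation p-value is 2/6 = 0.33. That floor binds a permutation test only; a t-test on the four site means can reject at 5%.
- *That the phase 3 intervals ignore site.* The article does not say how they are computed.
- *That baseline differences must be ordinary site variation.* Because recruiters know the allocation, selective recruitment is equally possible.

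**Conclusion.** The point holds in limited form. The planned baseline tests and ANOVA are patient-level methods in a trial that randomised four sites. For a single-time-point comparison, a nominal 5% t-test rejects about 6%, 10% and 16% of the time, and a 95% interval covers about 94%, 90% and 84%, at ICCs of 0.01, 0.05 and 0.10. These ICCs are assumptions. The direction of the error is certain for any positive ICC; its size cannot be fixed from the article. For the ANOVA interaction the fault depends on site-by-time variation, and for phase 3 on how the intervals are computed. This should be corrected before analysis, but it does not undermine the feasibility aims or the progression decision.

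**What to change.** 1. Delete the baseline chi-squared and t-tests. Tabulate baseline characteristics by arm and by site.
2. Report outcomes, EQ-5D-5L and costs descriptively by site and arm, without p-values.
3. If an interval for an arm difference is wanted, including in phase 3, compute it so that it accounts for site, for example from the four site means with t on 2 df. State the method.
4. Label any ICC estimate from four sites as highly imprecise.

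This changes the analysis wording only and needs no new patients, visits or data. The cost is that intervals for arm differences become at least about twice as wide (at least 1.36 SD against 0.64 SD), largely because only 2 df are available. Intervals that wide add little beyond the four site means, so purely descriptive reporting by site is a reasonable alternative.

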#### Qualitative analysis (phase 2)

The semi-structured interviews and/or focus groups will be recorded and transcribed verbatim. Inductive thematic analysis will be used to analyse the data collected. Thematic analysis will involve identifying and coding central themes within qualitative data through an iterative process [64]. To develop an understanding of the intervention, trial, context, and mechanisms of change, data analysis will be focused on answering these research questions [65]. Themes will be identified at a semantic level, in that they will develop from the explicit content contained within the data. This is different to identifying themes at a latent level, which requires a more hermeneutic approach [64]. Semantic themes are appropriate for a process evaluation as the aim is to gather explicit information on the implementation of an intervention and trial processes [66]. The importance of objective oversight has been highlighted in the MRC guidance on process evaluations, due to potential bias that researchers involved in the development of an intervention may bring when evaluating its acceptability [60]. In order to minimise risk of bias, investigator, method, and data source triangulation will be used to ensure validity of the identified themes [67]. Data will be managed using NVIVO 15.

#### Quantitative analysis (phase 3)

A cost-consequence analysis is recommended by the National Institute of Health Research for both complex interventions and feasibility studies where the outcomes of interest are not clear [68]. Costs and outcome measure data for both the intervention and control group will be presented using means and 95% confidence intervals to show a general overview of the economic costs of the intervention, and differences in resource use and outcome measures between groups. Completion rates and missing data for MODRUM [61] and the EQ-5D-5L [58] will be presented as frequencies to assess the feasibility of data collection.

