##### Quality of life

Health-related quality of life (HRQOL) has become increasingly important as an outcome measure of kidney replacement therapy, peritoneal dialysis, and transplant. HRQOL among haemodialysis patients has been shown to be lower as compared to pre-dialysis populations, the general population, and other chronic disease populations such as congestive heart failure, diabetes, depression, and even cancer. HRQOL is also poorer in cachectic patient populations and therefore an important criterion [10]. The 36-item Kidney Disease Quality of Life scale (KDQoL-36) will also be administered to patients in conjunction with EQ-5D-5L at baseline, post-intervention, and at 6 weeks and 3 months follow-up (this will be used in conjunction with Modular resource Use Measure (MODRUM), see phase 3). The EQ-5D-5L is recommended by the National Institute of Clinical Excellence (NICE) for deriving utility values for the calculation of quality adjusted life years in cost-effectiveness analysis within definitive economic evaluations [58] and has been shown to be a valid measurement of health status in patients receiving haemodialysis [59].

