##### Mortality

Survival will be recorded 6 and 12 months from the date of recruitment, and data will be generated from patients’ medical notes.

#### Phase 2

The process evaluation will follow the MRC guidance on process evaluations for complex evaluations [60] informed by the PRISM/RE-AIM framework [26]. It will therefore focus on the acceptability of the intervention, barriers and facilitators to implementation, the appropriateness of outcome measures, motivations for participation, reasons for continued engagement, and potential mechanism of impact of the intervention. The interviews will be conducted in person, and the guides will be flexible to ensure that participants can express and explore perspectives that they consider relevant to implementation. The interviews will be used to examine the fidelity and quality of implementation, and how the intervention effects are mediated by different settings and contexts. It will also examine acceptability and unintended consequences.

#### Phase 3

Healthcare resource use of patients will be collected using MODRUM [61]. This measure will collect information on health and social care service use pre and after the intervention. The measure will be used at baseline and 3 months follow-up. The outcome of interest will be the feasibility of using a healthcare resource use log in a full economic evaluation according to proportion of patients who complete the healthcare resource use log. The evaluation of costs related to the intervention and implementation, in addition to any operational costs, will provide important information on adoption and implementation in RE-AIM [27].

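### The phase 3 differences between groups in costs, resource use and EQ-5D-5L are planned with no baseline adjustment named, although MODRUM and EQ-5D-5L are both collected at baseline (minor)

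*Protocol article*

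**What the plan says.** The section Quantitative analysis (phase 3) chooses a cost-consequence presentation and names the statistic and its purpose: the economic data from both arms "will be presented using means and 95% confidence intervals to show a general overview of the economic costs of the intervention, and differences in resource". The sentence ends by making clear that service consumption and outcomes are to be compared across the two groups. Apart from counts of completion and missing data for the two instruments, this is the only analysis described there.

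The baseline values exist. For MODRUM, Data collection, Phase 3 states: "The measure will be used at baseline and 3 months follow-up". It adds that the instrument covers service use before and after the intervention. For EQ-5D-5L, the Quality of life section says that KDQoL-36 is given "in conjunction with EQ-5D-5L at baseline, post-intervention, and at 6 weeks and 3 months follow-up".

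On allocation, the Randomisation section reports two units per arm and says that "the personnel who will approach participants regarding the trial will have access to the random allocation sequence". The Abstract gives 10 patients per site. Strengths and limitations accepts that usual care may vary between sites and plans to record this in the process evaluation.

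By contrast, Quantitative analysis (phase 1) uses baseline values explicitly, through mean change and repeated-measures ANOVA.

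**The concern.** A between-group difference in costs or service use is to be shown with an interval, and the method named for it makes no use of the baseline value of the same measure. Four units is a small number to randomise. Two arms of two dialysis units can easily differ in prior service use or utility by chance, and recruiters who know the allocation could add to that through whom they approach. Part of any such gap would reappear in the follow-up difference.

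What is at stake is the precision and interpretability of a descriptive figure. MODRUM is not among the phase 1 outcomes, so the phase 3 section gives its data the only analysis they receive. A baseline-adjusted estimate would also show whether baseline MODRUM is complete and predictive enough to justify its burden in a definitive trial, which bears on objectives ii and iv.

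**Working it through.** **Plan's own figure.** 4 units × 10 patients = 40, that is 20 + 20 per arm. This reproduces the stated sample. The article gives no ICC, correlation, SD or power, so the ICC and r below are assumptions, shown over a range.

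**Step 1: likely size of the baseline gap.** With n = 20 per arm in units of m = 10, the SD of the chance difference between arm means at baseline, in patient-level SD units, is √[2 × (1 + (m − 1) × ICC) / n] = √[2 × (1 + 9 × ICC) / 20].

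| Assumed ICC | 1 + 9 × ICC | SD of baseline gap | Chance that the gap exceeds 0.3 SD |
|---|---|---|---|
| 0 | 1.00 | √0.100 = 0.32 | 34% |
| 0.05 | 1.45 | √0.145 = 0.38 | 43% |
| 0.10 | 1.90 | √0.190 = 0.44 | 49% |

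The last column is the two-sided normal probability, 2 × [1 − Φ(0.3 / SD)].

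**Step 2: how much carries over.** A plain follow-up difference inherits about r × gap. For a gap of one standard deviation at ICC 0.05 (0.381), this is 0.3 × 0.381 = 0.11, 0.5 × 0.381 = 0.19 or 0.7 × 0.381 = 0.27 SD units.

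**Step 3: what adjustment gains.** In large samples, the adjusted SD is the plain SD × √(1 − r²). At ICC 0.05 that is 0.381 × 0.954 = 0.36, 0.381 × 0.866 = 0.33 and 0.381 × 0.714 = 0.27. A simulation of 20,000 trials per setting (two plus two units of 10, no true effect, normal data, the same r at unit and patient level) gives slightly larger values, because the slope must be estimated:

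| ICC | r | SD, plain difference | SD, baseline-adjusted |
|---|---|---|---|
| 0.05 | 0.3 | 0.38 | 0.37 |
| 0.05 | 0.5 | 0.38 | 0.34 |
| 0.05 | 0.7 | 0.38 | 0.28 |
| 0.10 | 0.3 | 0.44 | 0.43 |
| 0.10 | 0.5 | 0.43 | 0.38 |
| 0.10 | 0.7 | 0.44 | 0.31 |

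At ICC 0.05 the relative reductions, from the unrounded SDs, are 1 − 0.368/0.381 = 3%, 1 − 0.340/0.384 = 11% and 1 − 0.276/0.378 = 27%.

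**Step 4: what adjustment does not do.** In the same simulation the plain difference averages about 0, so it is unbiased over repeated randomisations. Coverage of a patient-level 95% interval is about 0.89 to 0.90 at ICC 0.05 and 0.84 to 0.85 at ICC 0.10, with or without adjustment.

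**The case against.** The strongest reply is that this is a journal article describing a descriptive output of a feasibility study, and that covariate adjustment is often left to an analysis plan or health economics plan that is not shown. The sentence promises means and intervals, and it does not rule out an adjusted estimate. Phase 3 also has another target: "The outcome of interest will be the feasibility of using a healthcare resource use log in a full economic evaluation", judged by how many patients complete it. No progression criterion in the Discussion depends on a cost or utility difference. For EQ-5D-5L, its place among the phase 1 measures means that the change and repeated-measures analyses there may already use its baseline.

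Much of this stands, and it limits the point to a minor one. It does not remove it. The article goes beyond silence: it names a statistic and a between-group use for it in a section of its own, whereas the phase 1 section says explicitly how baseline enters. The phase 1 analyses do not extend to MODRUM.

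A reader might infer that the plan commits to raw follow-up means and will report baseline gaps as intervention effects. The text supports neither reading: it does not call the means raw or restrict them to follow-up, and it speaks only of differences between groups. A reader might also infer that randomisation was unstratified, but the Randomisation section does not say.

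**Conclusion.** The point holds as a minor one. The phase 3 section plans to show between-group differences and names no baseline adjustment, although the baseline values are collected in both arms. The consequence is exposure to chance imbalance and some lost precision. Systematic bias might be inferred, but the plain difference is unbiased over randomisations. Recruiters' knowledge of the allocation makes selection possible, and nothing in the article shows that it has happened.

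The gain depends on r: negligible at 0.3, modest at 0.5 and material at 0.7. These sizes rest on assumed ICCs and correlations and on normal data, and cost data may well be skewed. Adjustment does not make a patient-level interval valid with two units per arm. The case is strongest for costs and resource use and weaker for EQ-5D-5L.

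**What to change.** In Quantitative analysis (phase 3):

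- Keep the means by arm, and show them at baseline and at follow-up.
- Report the between-group difference in cost or resource use adjusted for baseline MODRUM cost or use, and the difference in EQ-5D-5L utility adjusted for baseline utility.
- Label both differences descriptive, and state that patient-level intervals do not reflect the clustering of patients in four units.

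This costs a sentence or two of text and two regressions on data already collected. The small downside is that patients without a baseline value drop out of the adjusted estimate, since the Missing data section rules out imputation; the number analysed should therefore be given beside each estimate.
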